### Sample size

The project funding agency requires a sample size of at least one-third of the potential PCPs (n = 379), which would capture roughly 2,500 patients with type 2 diabetes mellitus. This sample size allows 80% power (type II error: 0.20) to detect a 20% relative difference between the intervention arms in the proportion of patients achieving a 10% improvement in any one of the following: blood pressure, total cholesterol, or HbA1c (type I error: 0.05; assumed intracluster coefficient 0.6; [67] for calculation methods).

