### Primary and secondary endpoints

The primary endpoints of the study are the proportion of patients reaching ADA targets for three clinical outcomes: HbA1c < 7%; SBD ≤ 130 mmHg; and LDL-C < 100 mg/dl. Secondary endpoints are the mean improvements in individual values of 12 validated parameters: HbA1c, LDL-C, HDL-C, Total Cholesterol, SBP, DBP, weight, physical exercise, healthy diet, smoking status, and statin and anti-platelet therapy.

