### Statistical analysis

Statistical analyses will be performed using an intent-to-treat approach with a multilevel model. Linear and generalized linear mixed models will be used to account for the clustered nature of the data, *i.e*., patients clustered within PCPs, and repeated assessments clustered within patients. Such models measure how outcomes change over time within patients and whether these changes depend on patient and/or PCP's characteristics, such as the intervention program or DCT use (see hypothesis two). DCT use is defined as having at least one consultation with a member of the team besides the health psychologist and the traveling educator, which are only available for AQIP patients.

We will use generalized estimating equations (GEE), an extension of the quasi-likelihood approach, to test for differences in the evolution of the primary and secondary endpoints for all patients and within the intervention arms. For binary variables, we use the exponential inverse transformation to obtain the 95% confidence interval for the odds ratio.

Subgroup analyses (see hypothesis one) can distinguish intervention effects using different cut-off values. For HbA1C, three subgroups are defined: patients with HbA1c < 7%; HbA1c ≥ 7% and < 8%; and HbA1c ≥ 8%. For SBP, four subgroups are defined: patients with SBP ≤ 130 mmHg; SBP > 130 mmHg and ≤ 140 mmHg; SBP > 140 mmHg and ≤ 160 mmHg; and SBP > 160 mmHg. For LDL-C, four subgroups are defined: patients with LDL-C < 100 mg/dl; LDL-C ≥ 100 mg/dl and < 115 mg/dl; LDL-C ≥ 115 mg/dl and < 130 mg/dl; and LDL-C > 130 mg/dl.

Linear mixed models with subject-specific intercepts and slopes are used to test whether subject-specific evolutions are related to initial parameters. HbA1c will be transformed logarithmically to meet the parametric assumptions of the statistical models. All analyses will be performed using SAS, version 9.

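### The LDL-C subgroup rule assigns a value of exactly 130 mg/dl to no subgroup; only the LDL-C subgroup analysis is affected, and the effect is small

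*Protocol article*

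**What the plan says.** Under Statistical analysis, the protocol article introduces cut-off subgroups for three parameters and links them to its first hypothesis: "Subgroup analyses (see hypothesis one) can distinguish intervention effects using different cut-off values".

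- **LDL-C.** The article states "For LDL-C, four subgroups are defined". The first two are "patients with LDL-C < 100 mg/dl; LDL-C ≥ 100 mg/dl and < 115 mg/dl", and the last two are "LDL-C ≥ 115 mg/dl and < 130 mg/dl; and LDL-C > 130 mg/dl".
- **HbA1c.** Three subgroups: "patients with HbA1c < 7%; HbA1c ≥ 7% and < 8%; and HbA1c ≥ 8" per cent.
- **SBP.** Four subgroups, the upper two being "SBP > 140 mmHg and ≤ 160 mmHg; and SBP > 160 mmHg".

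No other section assigns an LDL-C of 130 mg/dl to a subgroup or says how a patient outside all four would be handled. The primary endpoints, under Primary and secondary endpoints, use a different LDL-C cut-off: "HbA1c < 7%; SBD ≤ 130 mmHg; and LDL-C < 100 mg/dl".

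**The concern.** A subgroup rule should place each patient with a value in exactly one subgroup. Here the third LDL-C subgroup excludes its upper limit and the fourth excludes its lower limit, and both limits are 130. The value 130 itself is left over.

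The article could have left the subgroup boundaries to a later document. It instead fixed each one with an explicit inequality sign, and one of them does not work as written.

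Two practical consequences follow. If the rule is programmed literally, the four LDL-C subgroups do not add up to all patients with an LDL-C value. If the programmer notices, 130 must be put in either the third or the fourth subgroup, and that choice is better settled in the text than made once data are in hand.

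**Working it through.** The plan states no figure on this point, so there is none to reproduce. The check has two parts.

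**1. Does each rule cover every value once?**

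Each rule was coded as written, and the number of subgroups containing each value was counted. A complete rule gives a count of 1 throughout.

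| Rule | Values tested | Values with a count other than 1 |
|---|---|---|
| LDL-C as written | 20–300 mg/dl, steps of 1 and of 0.1 | 130 only (count 0) |
| HbA1c as written | 4.0–15.9%, steps of 0.1 | none |
| SBP as written | 80–259 mmHg, steps of 1 | none |
| LDL-C, fourth subgroup changed to ≥ 130 | 20–300 mg/dl, steps of 1 | none |
| LDL-C, third subgroup changed to ≤ 130 | 20–300 mg/dl, steps of 1 | none |

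The value 130 is the only gap, and there are no overlaps. Either way of closing the boundary completes the rule. The LDL-C boundaries at 100 and 115 both put the boundary value in the upper subgroup, as the HbA1c boundaries do. SBP uses the opposite convention consistently, with the boundary value in the lower subgroup.

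**2. How many patients could this concern?**

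From the article (Sample size): a planned recruitment "which would capture roughly 2,500 patients with type 2 diabetes mellitus".

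Assumed, because the article gives none of it: LDL-C is Normal with mean m of 90 to 120 and SD s of 30 to 40 mg/dl, and every patient has a value.

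With recording in whole mg/dl, the share recorded as 130 is

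P = Φ((130.5 − m)/s) − Φ((129.5 − m)/s), and the number of patients is 2,500 × P.

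- Lowest case, m = 90, s = 30: Φ(1.350) − Φ(1.317) = 0.0055, giving 13.7 patients.
- Highest case, m = 120, s = 30: Φ(0.350) − Φ(0.317) = 0.0126, giving 31.4 patients.

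| Mean | SD 30 | SD 35 | SD 40 |
|---|---|---|---|
| 90 | 13.7 | 14.8 | 15.1 |
| 100 | 20.2 | 19.7 | 18.8 |
| 110 | 26.6 | 24.2 | 22.0 |
| 120 | 31.4 | 27.4 | 24.2 |

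The range is about 14 to 31 patients, or 0.5% to 1.3% of 2,500.

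With recording to 0.1 mg/dl, the limits become 129.95 and 130.05. The same grid then gives 1.4 to 3.1 patients, about 1 to 3.

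**The case against.** The strongest reply is that this is an editorial slip with little consequence. The sign > is most plausibly a mistake for ≥, and an analyst coding four subgroups would probably close the gap without comment. The subgroup analyses are worded as something that can be done, not as a required test. The size rests almost entirely on inputs from outside the article, and it depends most on recording precision, which the article does not state. All of this stands, and it limits the weight of the point. It does not make the rule complete as written.

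Three stronger readings are tempting and not supported:

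- **That these patients drop out of all the cut-off analyses, or out of the trial's main results.** The same patients are fully classified for HbA1c and SBP. The LDL-C primary endpoint is cut at 100 mg/dl, the secondary LDL-C endpoint is a mean improvement with no cut-off, and the planned mixed models relating patients' evolution to initial parameters do not depend on the 130 boundary. Nor does the article say that unclassified patients are excluded; that follows only from applying the rule literally.
- **That the gap biases the comparison of the arms.** If the subgroups are formed on baseline values, nothing in the article suggests that a reading of exactly 130 would be more common in one randomized arm than in the other. The loss shown is one of completeness and a little precision.
- **That the gap matters more because it lies beside the highest-risk patients.** The article gives LDL-C ranges and does not label any subgroup by risk.

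**Conclusion.** The point holds as a minor error in a stated analysis rule. An LDL-C of exactly 130 mg/dl belongs to none of the four subgroups, and a literal application leaves those patients out of the LDL-C subgroup analysis and out of nothing else.

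That the gap exists is certain from the text. Its size is not. The estimate of about 14 to 31 patients in whole mg/dl, or about 1 to 3 at 0.1 mg/dl, depends on the assumed Normal distribution, the assumed mean and SD, the planned 2,500 patients and complete LDL-C data. On any of these settings it is at most about 1.3% of patients, and no primary or secondary endpoint changes.

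**What to change.** Write the fourth LDL-C analysis subgroup as LDL-C ≥ 130 mg/dl. Changing the third subgroup to ≤ 130 would also close the gap, but ≥ 130 keeps the convention of the other LDL-C boundaries, in which each subgroup includes its lower limit and excludes its upper one.

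The cost is one character in the text, best changed before the subgroup analysis is programmed. It alters only how patients are grouped for analysis and leaves sample size, endpoints and treatment targets as they are.

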## Discussion

Trials of complex interventions inform the drive to provide the most cost-effective health care [7]. RCTs are recognized as the 'gold standard' methodology in quantitative research. Health care interventions are, however, often complex and are always implemented in complex health care settings [68-71]. Complex interventions often have particular characteristics that reduce chances of success in a RCT, including the incorporation of multiple components, targeting multiple outcomes, being difficult to implement or evaluate, or aiming to achieve outcomes that are notoriously difficult to influence [72]. In this context, the complexity of an intervention can present a substantial barrier to its adoption [73]. Complex interventions therefore have greater scope for variation in their delivery and are more vulnerable to one or more components not being implemented correctly [74].

Although we have not performed a pilot trial to assist in data interpretation or clarify process and outcome results, our stakeholder analysis informed our understanding of existing barriers to high-quality diabetes care and allowed us to incorporate innovative change interventions, such as interdisciplinary teams operating on the primary/specialty care interface and educational strategies that target changes in professional practice and improvements in patient empowerment [75]. These hypotheses will be tested using a large group of physicians and patients over an 18-month period. Most quality improvement programs include smaller target groups and shorter intervention periods of six months, which may not be long enough to completely remove the Hawthorne effect. Our study also targets the primary/specialty care interface, an important attribute of high-quality diabetes care [76]. In particular, the clinical leadership and coaching provided by a diabetologist to both the PCPs and the DCT is of particular importance in fragmented systems of care, such as in Belgium. We also explicitly focus on multiple cardiovascular risk factors as the primary outcomes, whereas other studies have not [77]. Finally, we incorporate all six dimensions of the CCM,, and are only the fourth study in diabetes care to do so [9,78,79]. The use of all six dimensions of the CCM permits evaluation of how CCM components are associated with improved outcomes to further refine the model. We therefore explicitly describe how the implementation strategies relate to every dimension of the CCM. Implementation strategies in complex interventions are rarely described [80], even in large-scale implementation studies, which limits the understanding of why an intervention is or is not locally successful [81].
